### Inclusion criteria

Proven tumour-free status (including participants who have undergone endoscopic polyp removal) among carriers of a germline pathogenic variant in one of MMR genes, specifically *MLH1*, *MSH2* (including *EPCAM*) or *MSH6*.

Male or female subjects aged over 30 years.Female participants who are postmenopausal for more than 1 year, or females of childbearing potential who are using a highly effective method of contraception (ie, oral hormonal contraceptives, hormone implants, hormone injections, sterilisation, hormonal or copper intrauterine device, sterilised/vasectomised partner or diaphragm combined with a condom, spermicide or birth control pills) or who agree to abstain from heterosexual activity during the treatment period. Females of childbearing potential must present a negative pregnancy test at both screening and randomisation.Signed written informed consent was obtained prior to study inclusion.

### Exclusion criteria

Presence of colorectal neoplasia that is benign but non-removable endoscopically (participants may be included if the adenoma is successfully removed).Carriers of germline variants in the *PMS2* gene.History of stage III or stage IV CRC.Presence of any metastatic disease.Regular use of acetylsalicylic acid (ASA or aspirin), defined as daily use of ≥100 mg for more than three consecutive months within the past year.Regular use of non-steroidal anti-inflammatory drugs (NSAIDs) or cyclooxygenase-2 inhibitor, defined as daily use for more than three consecutive months within the past year.Known hypersensitivity to 5-ASA.Participants who have undergone any subtotal or total colectomy.Surgery involving the colon or rectum within the previous 6 months.Unwillingness or inability to provide informed consent.Pregnant or breastfeeding women.Participation in another clinical study involving an investigational medicinal product (IMP) within 3 months prior to screening.Renal insufficiency, defined as a glomerular filtration rate <30 mL/min/1.73 m².Severe liver disease or liver failure, defined as an elevation of liver enzymes to more than three times the upper limit of normal.Current or historical serious psychiatric disorders or alcohol/drug abuse that, in the investigator’s opinion, may impact the assessment of IMP safety and efficacy or compromise protocol adherence.History of myocarditis or pericarditis.Any other severe acute or chronic medical conditions (eg, severe chronic lung disease, including chronic obstructive pulmonary disease or asthma; kidney disease; or heart disease), psychiatric disorders or laboratory abnormalities that may increase the risk of study participation or affect the ability to comply with study procedures or IMP administration. Such conditions, as judged by the investigator, would render the subject inappropriate for study entry.

### Study participants

Consistent with descriptive objectives, we will explore whether 5-ASA effects of mesalamine differ by major LS-genotypes. *PMS2* carriers were excluded a priori given their lower CRC-penetrance, later average age at onset and generally longer recommended colonoscopic surveillance intervals compared with *MLH1*, *MSH2*/*EPCAM* and *MSH6*. Consequently, the expected 24-month event rate among *PMS2* carriers is low; including this low-event stratum would dilute information and yield imprecise *PMS2*-specific estimates (ie, wide confidence intervals), thereby constraining interpretability. After database lock and unblinding, genotype stratified exploratory results and comment on their interpretability, in the light of observed event rates and multiplicity.

### Recruitment and study status

Following the second amendment (21 September 2021), and qualified person approval for IMP release (early 2022), the first participant was enrolled in March 2022. The study remains ongoing; EOT for the last enrolled participant is scheduled for Q3 2027. Originally planned as a European multicentre trial, the study was refocused to a Nordic multicentre trial for logistical reasons. Participating or planned sites are: Sweden-Karolinska University Hospital, Sahlgrenska University Hospital, Uppsala University Hospital, Norrlands University Hospital, Skåne University Hospital and Ersta Hospital; Denmark—Hvidovre University Hospital in Denmark.

### Patient and public involvement

*When and how were patients/public first involved in the research?* The Swedish patient organisation, *Magtarmförbundet*, participated in the study by disseminating informational materials to enhance participant recruitment through information sharing. Regular meetings were conducted with the involved patient representatives throughout the course of the study.

*How were the research question(s) developed and informed by their priorities, experience and preferences?* Patients with LS live with the awareness of a significantly increased risk of developing CRC. For these patients, identifying strategies to reduce this risk is a pressing priority. While the study’s objectives align with these patient priorities and were welcomed by *Magtarmförbundet*, patient representatives were not actively involved in the development of the research questions.

*How were patients/public involved in*

*The design and conduct of the study?* As noted above, patient representatives were not actively involved in the study design and its conduct.*Choice of outcome measures?* As noted above, patient representatives were not actively involved in selecting the outcome measures.*Recruitment of the study?* Patients played a role in participant recruitment by disseminating informational materials via patient organisations and by engaging with relatives, given the genetic predisposition associated with LS.

*How were (or will) patients/public be involved in choosing the methods and agreeing plans for dissemination of the study results to participants and linked communities?* Patient forums will be involved in the dissemination phase, offering information and hosting discussion meetings to facilitate knowledge transfer and further spread of findings. The study results will be published through Open Access to ensure broad accessibility and engagement with both participants and the wider community.

### Study completion

The study concludes with the final follow-up call of the last participant, with participant records monitored for 20 years postinclusion. Authorities will be notified within 90 days, or within 15 days if terminated early, with a summary report submitted within 1 year of study completion.

### Data statement section

Data collected at all visits are entered into an interactive form within 5 days after the participant’s visit. The case report form (CRF) has been verified following guidelines established before study onset as detailed in the Data Monitoring Plan (DMP). Maintenance of the study database will be performed by CTO, Center for Clinical Cancer Studies, Cancer Theme, Karolinska University Hospital, Stockholm, Sweden. Data will be collected using the electronic CRF (eCRF) system PheedIt, based on the SAS system provided by Region Stockholm, Stockholm, Sweden, and registered at Center for Clinical Cancer Studies (CTO), Cancer Theme, Karolinska University Hospital, Stockholm, Sweden. For each enrolled subject, an eCRF must be completed and electronically signed by the investigator or designated sub-investigator. Withdrawal reasons and incomplete assessments must be documented and verified in the eCRF by the investigator. Site staff authorised by the investigator will make entries and corrections, which will be monitored by the investigator for accuracy. Following database closure, a printout of completed eCRFs will remain on-site, with originals archived at the sponsor site poststudy. Details on the eCRF will be documented in a separate DMP provided by CTO, Karolinska University Hospital. The investigator must verify the accuracy of all eCRF data entries. The investigator will keep accurate and thorough records to ensure complete documentation of the study and to facilitate data verification, in accordance with International Counsil for Harmonisation’s Good Clinical Practice (ICH-GCP) guidelines. An interim analysis of cfDNA sampling, colonoscopy results, biomarkers and faecal samples will be conducted after two years for the first participant, with data unblinded only to the statistician.

### Statistics, sample size calculation

The statistical design of this trial was originally informed by findings from the CaPP2 trial.^5^ CaPP2 was a 2-year study that employed a 2×2 factorial design to evaluate the effects of resistant starch and aspirin (ASA). After a mean of 27 months on the study drug, 18.9% of participants had developed neoplasia by the second endoscopy. Based on similar inclusion and exclusion criteria, it was estimated that 20% of the placebo group in this study would present with neoplasms after 24 months. A clinically meaningful outcome would be a reduction in neoplasia risk to 7.5%, similar to the reduction observed in the CaPP2 trial. Sample size calculations were based on an assumption of a 20% neoplasia rate in the control group. To detect a reduction to 7.5% in the experimental group (HR 0.375), with a two-sided significance level of 5% and 80% power, a sample size of 236 participants was estimated. At the first interim analysis of the ongoing MesaCAPP (mesalamine for Colorectal Cancer Prevention Programme in Lynch syndrome) study, a higher-than-expected overall neoplasia rate of 50% was observed. This change, while holding other factors constant, would increase the power to detect group differences from 80% to 99.9% with a sample size of 236 participants. A power of 80% would now be achieved with 131 participants. Under more conservative assumptions (HR 0.5) and an increased projected neoplasia rate of 65%, 80% power could still be reached with 101 participants. The trial plans to assess 1000 individuals for eligibility, with an estimated 50% agreeing to participate. However, approximately 75% of those screened are expected to fail to meet the inclusion criteria, based on data from the initial screening period. A 10% drop-out rate is anticipated and accounted for in the sample size calculation. Counts of neoplasia per participant will be analysed using Poisson or negative binomial regression, adjusted for country and prior CRC; overdispersion will be assessed and negative binomial used if indicated. All primary analyses are prespecified; sensitivity analyses assess robustness to missing primary endpoint data (details in the SAP).

Intermittent ASA/NSAID exposure will be recorded for concomitant medication and safety monitoring; the primary analysis includes no prespecified modelling or adjustment for this exposure. If exposure patterns or merging evidence warrant, these data may be included in exploratory or sensitivity analyses.

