**Trial registration number:**

ClinicalTrials.gov: NCT04920149. EudraCT: 2019-003011-55. EU CT: 2024-514765-19-01.

STRENGTHS AND LIMITATIONS OF THIS STUDYA multicentre, randomised, double-blind, placebo-controlled, phase II trial with prospective surveillance delivers a rigorous framework and provides a unique opportunity to evaluate chemopreventive efficacy in LS.Genotype-defined LS carriers (*MLH1*, *MSH2/EPCAM* or *MSH6;* ACMG class 4/5), with genotype prespecified in analyses, that is, covariate/interaction, rather than as a randomisation stratum.Structured long-term follow-up with serial biospecimen collection enables high-resolution, exploratory, pharmacodynamic, microbiome and inflammatory biomarker analyses under harmonised standard operating procedures.Recruiting this rare, genotype-defined cohort across Nordic centres strengthens generalisability, with coordinated oversight—positioning the trial to deliver reliable, broadly applicable evidence.With n=150 and observed event rates, precision for modest effects and subgroup estimates is limited; however, the study retains robust power for the end of treatment primary analysis.

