### Primary endpoint

The occurrence of colorectal neoplasia (both benign and malignant tumours) in the two groups is presented as absolute frequencies and percentages, accompanied by 95% CIs. Logistic regression is used to assess differences in neoplasia occurrence between the active treatment and placebo groups, adjusted for country and prerandomisation cancer history. Treatment effects are expressed as ORs with corresponding 95% CIs.

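### The 131 participants quoted for 80% power do not follow from the stated effect of 0.375; the figure matches a hazard ratio of 0.5, the value the next sentence introduces as more conservative

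*Protocol article*

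**What the plan says.** All the sizing figures stand in one paragraph of the protocol article, under Statistics, sample size calculation.

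- Starting point: "Sample size calculations were based on an assumption of a 20% neoplasia rate in the control group". The target is given as "To detect a reduction to 7.5% in the experimental group (HR 0.375), with a two-sided significance level of 5% and 80% power", which leads to 236 participants.
- Update: an interim look found neoplasia in 50% of participants, both arms together. The article says that nothing else is changed and that power at 236 rises from 80% to 99.9%. It then states: "A power of 80% would now be achieved with 131 participants".
- Further scenario: "Under more conservative assumptions (HR 0.5) and an increased projected neoplasia rate of 65%, 80% power could still be reached with 101 participants".
- Loss: the same paragraph says that a 10% drop-out is already allowed for.

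The section Study design plans 150 participants, 75 per arm. Under Primary endpoint, "Logistic regression is used to assess differences in neoplasia occurrence between the active treatment and placebo groups", with the result given as an odds ratio. The strengths and limitations box says that with 150 participants "the study retains robust power for the end of treatment primary analysis".

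**The concern.** The 99.9% and the 131 appear in adjacent sentences as two results of the same change. A reader will take both as figures for the effect of 0.375, and will take the HR 0.5 sentence as a separate check with a weaker effect. If 131 already assumes 0.5, the effect behind the required size has moved from 0.375 to 0.5 without the text saying so, and the apparent robustness check relaxes nothing except the event rate, which it raises.

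The scale adds to the problem. The paragraph uses the label HR throughout, while the primary analysis is a logistic regression on a binary outcome. What 0.375 or 0.5 means for the risk in each arm is not stated, and power depends on it.

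**Working it through.** **Inputs.** Two-sided 5%, 80% power, 20% vs 7.5%, effects 0.375 and 0.5, rates 50% and 65%, N of 236, 131 and 101, and 10% loss (all from the sample size section); 150 randomised 1:1 (Study design). z-values are 1.960 and 0.8416; the square of their sum is 7.849.

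**1. The 236 reproduces as a two-proportion figure.** Per arm, n = [1.960·√(2p̄(1−p̄)) + 0.8416·√(p₁(1−p₁)+p₂(1−p₂))]² / (p₁−p₂)². With 0.20 and 0.075 this is 117.96, so 118 per arm and 236 in total, with no drop-out added. Here 0.375 = 7.5/20 is a risk ratio. The hazard ratio for the same two risks would be ln(0.925)/ln(0.80) = 0.35, and the odds ratio 0.32.

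**2. The 99.9% at 236 reproduces with 0.375.** Log-rank: 236 × 0.5 = 118 events; power = Φ(½·√118·|ln 0.375| − 1.960) = 99.96%. Two proportions, 50% vs 18.75%: 99.95%. With HR 0.5 the log-rank power would be 96.4%.

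**3. The 131 does not reproduce with 0.375.** Log-rank events = 4 × 7.849 / (ln HR)².

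| Reading of 0.375 at 50% | N for 80% power | Power at 131 |
|---|---|---|
| Log-rank, 32.63 events / 0.50 = 65.3 | 66 | 97.8% |
| Risk ratio, 50% vs 18.75% | 72 | 97.2% |
| Hazard ratio on a 50% control rate, 50% vs 22.9% | 98 | 90.6% |

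In the last row, 22.9% = 1 − 0.5^0.375.

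**4. Check without choosing a formula.** For a fixed effect the standardised effect grows with √N.
- From 99.9% at 236: N for 80% = 236 × (2.802/5.050)² = 72.6. Rounding of the 99.9% allows 67 to 76.
- From 80% at 131: power at 236 = Φ(2.802 × √(236/131) − 1.960) = Φ(1.800) = 96.4%.

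So the two figures belong to different effects.

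**5. What does give 131 and 101.** For HR 0.5 the log-rank formula needs 65.35 events.
- 65.35 / 0.50 = 130.7, so 131.
- 65.35 / 0.65 = 100.5, so 101.

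Other routes come near 131: 50% vs 25% with continuity correction (132), 50% vs 25% with 10% loss (129), and 0.375 read as an odds ratio at an overall 50% (134). The first two also use a halving. The third gives 96.3% at 236, not 99.9%. None of them gives 101 for HR 0.5 at 65%.

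**6. Power of the binary comparison at the planned size.** 150 × 0.9 = 135 evaluable; two-proportion test, effect 0.5:

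| Reading of 0.5 | Arm risks | N for 80% | Power at 135 |
|---|---|---|---|
| Hazard ratio, control rate 50% | 50% vs 29.3% | 174 | 70% |
| Hazard ratio, pooled rate 50% | 61.8% vs 38.2% | 140 | 79% |
| Risk ratio, control rate 50% | 50% vs 25% | 116 | 86% |
| Hazard ratio, pooled rate 65% | 77.5% vs 52.5% | 114 | 87% |

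A risk ratio of 0.5 at a pooled 50% (66.7% vs 33.3%) would give 98%. For 0.375, 135 evaluable give about 91% (50% vs 22.9%) to 98% (50% vs 18.75%).

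**7. Drop-out.** 131 / 0.9 = 145.6, so 146, just under 150.

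**The case against.** Four points count on the other side.

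- **The trial may be large enough.** For the effect as worded, 131 is more than is needed, and 135 evaluable give 91% to 98% power. A reader might infer from the wrong figure that the trial is underpowered. The documents do not support that: even at 0.5 the result depends on a conversion that they do not give. This stands.
- **The log-rank source is inferred.** The article names no formula, and it condenses a full protocol that may name one. This stands as a limit. The conflict between 99.9% at 236 and 80% at 131 does not depend on it, and one formula yields both printed figures exactly.
- **No single corrected number follows.** It is tempting to replace 131 by 140 and 101 by 114. That would treat 0.5 as a true hazard ratio acting on a pooled rate, while reading 0.375 in the same paragraph as a risk ratio. For a rate of 50%, other readings of 0.5 run from about 70 to 174. The objection is right, so 140 and 114 are shown only as cases in a range.
- **The 150 and the drop-out.** A reader might conclude that 150 was derived from 131, or that the 10% loss was left out. The article never derives 150, and 131 inflated for loss is 146, so 150 can cover it. Only the superseded 236 clearly lacks the inflation. What remains is that the text does not say at which step the loss enters.

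The 101 case is also not a mere repeat of the 131 case, since its event rate rises from 50% to 65%. The fair criticism is that the effect of 0.5 is not new there.

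**Conclusion.** The figure of 131 is wrong as written. For the stated effect at a 50% rate the requirement is about 66 (log-rank), 72 (risk ratio) or 98 (hazard ratio on a 50% control rate), and no common effect gives both 99.9% at 236 and 80% at 131. The last of the three readings also gives 99.3%, not 99.9%, at 236. By strong inference, 131 and 101 are both log-rank figures for HR 0.5, so the cautious effect is already in the 131.

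The effect label is also mixed: 236 rests on a risk ratio, 131 and 101 most likely on a hazard ratio, and the analysis reports an odds ratio. At the planned size the power for an effect of 0.5 is therefore a range, about 70% to 87% over the four conversions tabulated (98% on the further reading). This assumes 135 evaluable and an unadjusted two-proportion test as a stand-in for the logistic regression. The unqualified statement on robust power is firmer than that range allows, although the same sentence already concedes limited precision for modest effects. The defect lies in the stated justification; it does not show that the planned size is inadequate.

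**What to change.** Revise the sample size paragraph as follows.

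1. Either label 131 with the effect it assumes (HR 0.5, if the sponsor confirms this), or replace it with the figure for 0.375, about 66 to 98 with the scale stated.
2. Call 0.375 a risk ratio.
3. Give the formula and the two arm proportions behind 131 and 101. Say that the 101 case differs from the 131 case in event rate only, if that is confirmed.
4. State power for the binary primary analysis at 150 randomised and 135 evaluable, as a range over named arm proportions.
5. Say at which step the 10% drop-out enters.
6. Qualify the statement on power in the strengths and limitations box to match.

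The cost is wording and a short recalculation. No extra participants are needed, and neither the design nor the analysis changes.

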### Ethics and dissemination

The study protocol was approved by the Swedish Ethical Review Authority (2019–04318) on 23 October 2019, with subsequent amendments approved on 26 April 2021 (2021-01570), 21 September 2021 (2021-04234) and 6 May 2024 (2024-02993-02). Approval was also obtained from the Danish National Medical Research Ethics Committee (2022021008) on 30 March 2022, with an amendment approved on 20 August 2024 (112356).

The protocol published here represents the version, which has been transitioned to the European Clinical Trials Information System in 2024. The trial is registered with ClinicalTrials.gov (NCT04920149) and EudraCT (2019-003011-55).

The investigator will ensure that this study adheres fully to the principles of the Declaration of Helsinki (as amended at the 56th WMA General Assembly, Tokyo, 2008), as well as to the laws and regulations of the country where the clinical research is conducted. Only appropriately trained personnel will participate in the study. All procedures will comply with ICH GCP Guidelines and, if applicable, the Code of Federal Regulations (USA), or other relevant national GCP guidelines. Accordingly, this study follows the Clinical Trials Regulation EU No 536/2014. Compensation for study-related injuries will be provided in accordance with applicable regulations. Study results will be disseminated through publication in peer-reviewed journals and presentations at scientific conferences.
